## Abstract

**Background:**

Linear endoscopic ultrasonography (EUS) allows the visualization, identification, and characterization of the extent of lesions of the gastrointestinal (GI) tract and adjacent structures. EUS-guided fine-needle aspiration (EUS-FNA) facilitates a more accurate diagnosis of mediastinal, intra-abdominal, and pancreatic lesions through the collection of the cytological material under direct visualization. Recent reports suggest that histological samples can be obtained by EUS-FNA with a reverse, bevel-tipped needle (the ProCore needle) to collect the core samples (fine needle biopsy, FNB), thereby adding a new dimension to the diagnostic usefulness of this technique. Certain neoplasms, such as lymphoma and stromal tumors, can be assessed by EUS-FNB to confirm the diagnosis. Here, we aimed to carry out a prospective, multicenter, single-blind, randomized, controlled trial to compare EUS-FNB and EUS-FNA.

**Methods/design:**

A total of 408 patients will be enrolled from five endoscopic centers. Patients will be divided into two groups: (1) group A, which is the EUS regular needle group (EUS-FNA) and (2) group B, which is the EUS ProCore needle group (EUS-FNB). Patients in group A will be examined with a 22G EchoTip Ultra needle, and patients in group B, with a 22G EchoTip ProCore needle. For all included patients, four EUS-guided passes will be made in each lesion. In the first and second pass, a slow-pull suction method of the stylet will be done. The third and fourth pass will use manual suction of 5 cc. The primary objective is to compare the diagnostic yield of malignancy by EUS-FNA versus EUS-FNB.

**Discussion:**

The trial will compare samples obtained by EUS-FNA versus EUS-FNB for the diagnostic yield of solid lesions. The efficacy of these two sampling methods will be assessed on various lesions, which may provide insights into developing practice guidelines for their future indications.

**Trial registration:**

Clinical Trials.gov, NCT02327065.

## Background

Linear endoscopic ultrasonography (EUS) allows the identification of suspected malignancies by creating real-time images of the digestive tract and adjacent lesions [1]. EUS-guided fine needle aspiration (FNA) offers an opportunity for sampling mediastinal, intra-abdominal, and pancreatic lesions under direct visualization [2]. Since its original description in the early 1990s, EUS-FNA has been used to obtain cytological material, thereby contributing to the prompt and accurate diagnosis of clinically suspected lesions [3–6]. The diagnostic accuracy of EUS-FNA is generally high, from 52 % to 94 % [7–10]. Cytopathology plays an important role in improving the diagnostic yield. Notably, distinguishing the inflammatory lesion caused by a reaction and regeneration from well-differentiated neoplasia solely based on cytological evaluation can be difficult. Moreover, certain neoplasms, such as lymphoma and stromal tumors, require histological exams to assess the tissue architecture and cell morphology changes in order to confirm the diagnosis [11]. To overcome this limitation, a new fine needle biopsy (FNB) device has been designed (Cook Endoscopy, Limerick, Ireland). The new ProCore needle was designed with a reverse bevel at the tip to collect a core sample. A multicenter study on 114 patients showed that the application of the ProCore needle (EUS-FNB) led to 85.96 % diagnostic accuracy; 90.2 % sensitivity to malignancy, 99 % specificity, 100 % positive predictive value (PPV), 78.9 % negative predictive value (NPV), and 92.9 % accuracy [11]. Overall, most studies favored EUS-FNB for achieving an adequate histological specimen and high diagnostic yield compared to EUS-FNA [11–16]. However, several studies have suggested that the diagnostic yields of EUS-FNB and EUS-FNA were similar [17–19]. Therefore, the impact of the needle type (ProCore or regular) on the diagnostic yield needs to be further studied. We plan to carry out a randomized controlled trial to compare the diagnostic yield of EUS-FNA versus EUS-FNB and to assess the sample quality obtained by both the slow-pull and the suction approaches.

## Methods/design

The study was approved by The Ethics Committee of Tongji Medical College, Huazhong University of Science and Technology (HUST) (IORG No: IORG0003571). Informed consent will be obtained from the patients or from their closest relatives with authorization.

### Study design

A total of 408 patients from five endoscopic centers in China will be enrolled in this prospective, multicenter, randomized, controlled trial. They will be randomly divided into two groups: (1) group A, which will receive the EUS procedure using the regular needle (EUS-FNA, 22G EchoTip Ultra needle, Cook Endoscopy, Limerick, Ireland) and (2) group B, which will receive the EUS procedure using the ProCore needle (EUS-FNB, 22G EchoTip ProCore needle, Cook Endoscopy, Limerick, Ireland). The recruitment process flowchart is shown in Fig. 1.

**Fig. 1 Fig1:**
[figure not shown]
CONSORT flowchart illustrating the randomization and recruitment process in the study. ^1^ Each slide will be assessed by two independent experts. The cytologists and pathologists will follow the protocol to assess the samples and will be blinded as to which technique is used for which specimen. ^2^ If diagnostic failure occurs, the patient will be allowed to crossover to the other group after agreeing to accept a needle biopsy again on the same lesion 1 week later. ^3^ Three follow-up points are scheduled after the biopsy (1-week postoperational follow-up, 12-week follow-up, and 48-week follow-up); thereafter, the follow-ups will be conducted via telephone interviews or outpatient interviews. Once the surgical pathologic results are obtained, we will stop the follow-up

### Objectives

The primary objective of this study is to compare EUS-FNA versus EUS-FNB for the diagnostic yield (%) of malignancy [13]. The secondary objectives are to compare EUS-FNA versus EUS-FNB for 1) the overall diagnostic yield (%) from solid lesions; 2) the diagnostic yield (%) from pancreatic and nonpancreatic solid lesions, 3) the crossover diagnostic yield (%), and 4) the sample quality obtained by either the slow-pull or suction approaches, respectively.

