#### Data analysis

A two-tailed distribution will be used and a *P*-value < 0.05 is considered statistically significant. Continuous variables will be measured as mean (range) and standard deviation using *t* tests or Wilcoxon rank-sum tests. Categorical variables will be measured as the count and percentage using the χ2 test. The diagnostic yield will be described as a proportion using the χ2 test; the blood contamination and cellularity in specimens with slow-pull and suction will be divided into three levels (Grade A, Grade B, and Grade C), and McNemar’s test for correlated proportions will be used. All analyses will be performed with SAS version 9.2.

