The success of EUS-FNA is associated with several factors, including appropriate methods of biopsy, sample preparation, and onsite cytopathological interpretation [31]. The onsite cytopathological interpretation may not always be available during EUS**-**FNA procedures; therefore, appropriate methods of biopsy and sample preparation are very important. Some echoendoscopists use slow-pull, and others use constant suction. Suction with a self-retracting syringe will likely bring more cellularity but also more blood. In this trial, the echoendoscopist will use both methods (slow-pull and constant suction) on each lesion and, hopefully, will be able to draw a clear conclusion on selecting which biopsy method should be used for which procedure. Furthermore, standard procedures and sample preparation methods will be used to process all types of biopsy samples. For example, after the needle has been inserted into the mass, for both FNA and FNB, the needle will be moved back and forth 20 times within the lesion to collect specimens. The specimens will be expelled from a needle in three steps: step 1, which involves pushing the stylet into the needle; step 2, which involves flushing the needle with 0.1 ml saline; and step 3, which involves filling the needle with 2 ml of air.

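### The one test named for the sample-quality grades compares techniques within a lesion, while secondary objective 4 compares needles; the needle comparison is left to an order-blind χ2 test and the needle-by-technique question to no stated test

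*Protocol article*

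**What the plan says.** All four secondary objectives share one stem in the Objectives section: "The secondary objectives are to compare EUS-FNA versus EUS-FNB for". Item 4 under that stem is "the sample quality obtained by either the slow-pull or suction approaches, respectively". Read together, they ask for FNA against FNB on sample quality, once for slow-pull and once for suction.

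The Data analysis section treats these grades separately. It says that "the blood contamination and cellularity in specimens with slow-pull and suction will be divided into three levels" and that "McNemar’s test for correlated proportions will be used". Its general rule for other categorical data is "Categorical variables will be measured as the count and percentage using the χ2 test".

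The Discussion explains that "the echoendoscopist will use both methods (slow-pull and constant suction) on each lesion", and hopes in this way to "draw a clear conclusion on selecting which biopsy method should be used for which procedure".

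Under Interventions, 204 patients are allocated to each needle. The technique section gives two slow-pull and two suction passes per lesion.

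**The concern.** The text contains three different questions:

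1. Do the needles differ in sample quality (Objectives)?
2. Do the techniques differ in sample quality (Data analysis)?
3. Does the better technique depend on the needle (Discussion)?

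The test named for the grades serves only the second question, and it is written for two outcome levels rather than three. The first question is the one protected by randomisation, and its test has to be inferred from a general rule that discards the grade order. The third has no stated test.

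If this stands, the needle comparison loses some efficiency. The technique comparison cannot be run as written without a further choice, such as a cut-point or an extension of McNemar's test, and that choice could be made after the grades are seen. Any advice on technique by needle would have no formal basis.

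**Working it through.** The plan gives no figure for objective 4, so there is none to reproduce. The allocation of 204 per arm comes from the plan; every grade distribution below is an assumption.

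**Step 1: match each question to a stated test.**

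| Question | Data structure | Test in Data analysis |
|---|---|---|
| FNA vs FNB, per technique | independent groups, three ordered grades | none by name; general χ2 rule applies |
| Slow-pull vs suction | paired within lesion, three ordered grades | McNemar (paired, binary) |
| Does the technique effect differ by needle? | difference between arms in a within-lesion contrast | none |

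**Step 2: what McNemar's test can see.** It uses only lesions whose two techniques disagree, so a needle effect that is equal under both techniques cancels. This was simulated with 204 per arm, 4,000 runs, the grade reduced to A versus other, and a within-lesion latent correlation of 0.5. McNemar's test was pooled over arms.

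| Assumed grade-A rates (slow-pull/suction) | McNemar, pooled | χ2 between needles, slow-pull samples | Interaction test |
|---|---|---|---|
| FNA 50/50 %, FNB 65/65 % | 5.2 % | 86 % | 4.7 % |
| FNA 50/60 %, FNB 60/50 % | 4.2 % | 54 % | 94 % |
| Both 50/60 % | 94 % | 4.8 % | 5.0 % |

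Each test detects its own effect. In row 1, McNemar's test rejects at about its null rate although the needles differ by 15 points. In row 2, pooled McNemar misses technique effects that run in opposite directions.

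**Step 3: the cost of ignoring order in the needle comparison.** Assume grades A/B/C of 45/30/25 % with one needle and 55/27/18 % with the other, a 0.25 SD shift on a latent normal scale. The χ2 noncentrality is n × Σ(p − q)²/(p + q):

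204 × (0.10²/1.00 + 0.03²/0.57 + 0.07²/0.43) = 2.04 + 0.32 + 2.32 = 4.69

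On 2 df at the 5 % level this gives about 48 % power. Simulation with 40,000 replicates gives 48 to 49 % for χ2 and 59 % for the tie-corrected rank-sum test. Other shifts:

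| Shift | χ2, 2 df | Rank-sum |
|---|---|---|
| 0.20 SD | 33 % | 42 % |
| 0.25 SD | 49 % | 59 % |
| 0.30 SD | 65 % | 75 % |

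**Step 4: three levels against a binary test.** McNemar's test has 1 df on a 2 × 2 table. The paired grades form a 3 × 3 table. Symmetry on that table is Bowker's test (3 df), and marginal homogeneity is Stuart-Maxwell (2 df). The 5 % critical values are 3.84, 5.99 and 7.81 for 1, 2 and 3 df, so the choice matters, and the article neither makes it nor gives a cut-point.

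**Step 5: power of the interaction test.** In row 2 of step 2 the technique effects differ by 20 points and power is 94 %. That implies a standard error of about 0.20/(1.96 + 1.58) = 0.0565. A 10-point difference is then 0.10/0.0565 = 1.77 standard errors, with power of about P(Z > 1.96 − 1.77) = 42 %.

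**The case against.** **The needle comparison does have a test.** A reader might infer that neither the needle question nor the technique-by-needle question has a usable test. For needles, the documents do not support that. The grades are categorical, the arms are independent, and the general χ2 rule gives a valid test for each technique. What remains is a loss of efficiency, on assumed distributions, for an endpoint that the plan does not power. A needle difference that is not monotone across the grades could even favour χ2.

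**Sample quality may be meant as a technique question.** The Background presents it as an assessment of slow-pull and suction, and on that reading a paired method is the right family. The Objectives section still places it under a needle-against-needle stem, and the Discussion refers to needle types and methods together. The readings need reconciling, and the binary-versus-three-level problem stands under either.

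**The matching of technique to needle is a hope in the Discussion, not an objective.** This is true, and an interaction test could be in an analysis plan that is not shown. But the article does choose a test for these grades, and that choice cannot support the conclusion hoped for.

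**False needle-specific indications.** One might argue that if the technique effect were the same with both needles and each arm had 50 % power, the two within-arm tests would disagree in 2 × 0.5 × 0.5 = 50 % of trials (42 % at 70 % power), and that the plan would read this as a needle-specific result. The arithmetic is right, but the article does not say that McNemar's test is run per arm rather than pooled, and nowhere plans to contrast a significant arm with a non-significant one. The figure shows why an interaction test is wanted; it is not an error rate of this plan.

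**Conclusion.** The point holds as a mismatch between objective, named test and intended conclusion, not as the absence of any usable test. Three things are established from the text:

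- McNemar's test cannot answer objective 4 as worded.
- It is specified for grades with three levels without a cut-point or an extension.
- No stated test covers the needle-by-technique question.

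The needle comparison remains valid under the general χ2 rule. Ignoring order costs about 10 percentage points of power (49 % against 59 %), given 204 per arm, the assumed grades and a uniform latent shift of 0.25 SD. The loss is 9 to 10 points across shifts of 0.20 to 0.30 SD. The primary objective is untouched. The change is worth making because it improves the analysis of data already being collected.

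**What to change.** State which comparison uses which test:

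- **(a) Needles.** Compare FNA with FNB by an ordered two-sample test (Wilcoxon rank-sum or row-mean-score CMH), separately for slow-pull and for suction samples.
- **(b) Techniques.** Compare slow-pull with suction by a paired ordinal test within lesion, in place of McNemar's test on three levels. Say whether it is pooled over needles or run per needle.
- **(c) Technique by needle.** Base any statement about which technique suits which needle on a needle-by-technique interaction test, not on separate within-arm P-values. An ordinal GEE or mixed model with lesion as cluster would do. It takes both passes per technique as they are and avoids subtracting grades, which would treat A to B and B to C as equal steps.

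Tests (a) and (b) also need a stated rule for reducing the two passes per technique to one grade, unless they are taken from the same clustered model.

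The cost is analysis wording, with no new patients or samples. The interaction test has modest power (about 42 % for a 10-point difference in technique effect under the assumptions above), so needle-specific claims become harder to make.

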### Setting

A total of 408 patients will be recruited from five endoscopic centers, including Tongji Hospital, Tongji Medical College, HUST, Wuhan; Cancer Institute & Hospital, Chinese Academy of Medical Sciences, Peking Union Medical College, Beijing; Fudan University Shanghai Cancer Center, Shanghai Medical College, Fudan University, Shanghai; Sun Yat-sen University Cancer Center, Guangzhou; and the First Affiliated Hospital, College of Medicine, Zhejiang University, Hangzhou. All clinic sites meet the following criteria: (1) at least 48 patients can be recruited per site; (2) at least 2 to 4 trained physician(s) and nurse practitioner(s) per center can participate in the trial; and 3) the site agrees to strictly abide by the study protocol.

### Eligibility

#### Inclusion criteria

Patients who meet the following inclusion criteria will be recruited to the trial:Age > 18 years oldSex: male or femalePatients who require endoscopic ultrasound and tissue sampling after imaging examination (MRI, CT, and ultrasonography) that shows either pancreatic, intra-abdominal, mediastinal, or pelvic cavity solid lesions (size > 1 cm)Patients who are willing to be examined in the trial centersPatients who are able to give consent

#### Exclusion criteria

Patients will be excluded from the trial for any of the following reasons:Hemoglobin ≤ 8.0 g/dLPregnant femalePatient has any coagulation disorder (PLT < 50,000/mm^3^, INR > 1.5)History of taking oral anticoagulation agents such as aspirin, warfarin, etc. in past weekExperienced acute pancreatitis in past 2 weeksHas cardiorespiratory dysfunction that cannot tolerate the operationHas mental diseases or drug addictionUnable to provide informed consent

### Randomization and blinding

The randomization will be conducted at the study office at the School of Public Health, Tongji Medical College, HUST. A stratified block randomization will be used, and the block size is 8. The patients will be allocated randomly to either group A (EUS-FNA) or group B (EUS-FNB) (1:1).

A data manager, who will not be involved in the data analysis or patient enrollment, will generate the randomization schedule. To ensure allocation concealment, the randomization schedule will be sealed under scratch cards (001–408). The scratch cards will not be opened until the baseline assessment is completed and the patient has consented to participate in the study.

The randomization schedule will not be available to the study recruiters or echoendoscopists until the baseline assessment is completed. Only the study coordinators have access to the randomization schedule. The cytologists and pathologists will be blinded during the entire study.

### Interventions

Patients will be allocated randomly into group A (EUS-FNA, n = 204) or group B (EUS-FNB, n = 204). Group A patients will be examined with the 22G EchoTip Ultra needle, and group B will be examined with the 22G EchoTip ProCore needle.

The procedure will be performed under deep sedation according to the principles of “monitored anesthesia care.” The patients will be anesthetized with intravenous administration of propofol by trained anesthetists. All patients will receive oxygen during the procedures; blood pressure and heart rate will be monitored. Once the lesion is evaluated by EUS, the echoendoscopist will select the shortest pathway, while avoiding blood vessels, to reach the lesion. Under real-time visualization, each lesion will be punctured with four needle passes. To eliminate technical biases, the same procedure for obtaining samples will be applied to each patient undergoing EUS-FNA or EUS-FNB.

### Technique for EUS-FNA and EUS-FNB

**1) The first and second needle passes (slow pull)** [20]: The needle will be advanced into the lesion under real-time EUS visualization. Back and forth movements will be made 20 times within the lesion and will be performed using simultaneous minimal negative pressure by pulling the needle stylet slowly and continuously.

**2) The third and fourth needle passes (5-ml suction)** [18]: After the needle has been advanced into the lesion under real-time EUS visualization, the stylet will be removed. Continuous suction will be applied with a 5-ml syringe, and the needle will be moved back and forth 20 times within the lesion. Suction will be released, and then, the needle will be withdrawn from the lesion.

After biopsy, the samples will be labeled immediately with numbers in the order of the needle pass. Samples will be prepared for histological and cytological examinations. The cytologists and pathologists will always be blinded regarding which technique was used for which specimen.

After the selected lesion has been punctured during the four needle passes, if no core tissue is obtained or if the operators determine the specimens are insufficient according to the results of the macroscopic onsite evaluation (MOSE) [21], the operators will use a proper puncture method to obtain samples as the backup procedure.

If diagnostic failure occurs, the patient will crossover to the other arm after agreeing to accept a needle biopsy again on the same lesion 1 week later with the same method mentioned above.

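### Slow pull is always passes 1–2 and suction always passes 3–4, so the planned slow-pull versus suction test estimates technique plus pass order and cannot by itself select a technique

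*Protocol article*

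**What the plan says.** **Sequence.** The Technique section sets "The first and second needle passes (slow pull") and "The third and fourth needle passes (5-ml suction"), each pass with 20 movements of the needle. The Abstract gives the same order: "The third and fourth pass will use manual suction of 5 cc".

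**Who gets it.** Under Interventions, "the same procedure for obtaining samples will be applied to each patient undergoing EUS-FNA or EUS-FNB". A crossover biopsy after diagnostic failure repeats the same method.

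**What is randomized.** Needle type only: "The patients will be allocated randomly to either group A (EUS-FNA) or group B (EUS-FNB) (1:1"). The article does not randomize, alternate or counterbalance the order of techniques.

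**What is compared.** The fourth secondary objective concerns "the sample quality obtained by either the slow-pull or suction approaches, respectively". Data analysis assigns McNemar's test to the blood contamination and cellularity grades under slow pull and suction. The Discussion hopes that using both methods on each lesion means the endoscopist "will be able to draw a clear conclusion on selecting which biopsy method should be used for which procedure".

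**The concern.** A paired comparison within a lesion removes differences between lesions. It does not remove differences between the first half and the second half of the sampling session. Here suction always enters a lesion that has already had two passes, or 2 × 20 = 40 needle movements. If earlier passes cause bleeding or deplete tissue, later samples would differ whichever technique was used, and McNemar's test would credit the difference to suction.

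The Discussion already expects suction to bring more cells and more blood. An order effect towards more blood would therefore look like confirmation of that expectation. What is at stake is a practice recommendation on sampling technique. The trial's main conclusion is not at stake.

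**Working it through.** The article gives no sample size, expected difference or order effect for slow pull versus suction. Its one sample-size calculation concerns the primary comparison and plays no part here, so there is no figure of the plan's own to reproduce.

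**1. What the contrast estimates.** Let T be the suction-minus-slow-pull effect and O the effect of being in passes 3–4 rather than 1–2.

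- All patients have slow pull in passes 1–2 and suction in passes 3–4, so the expected paired difference is T + O.
- If half had the reverse order, their expected difference would be T − O, and the average over both halves would be T.
- No patient has the reverse order, so T and O cannot be separated without a further assumption.

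**2. What is not affected.** For FNA versus FNB, O is present in both arms. It cancels if it is the same with both needles. If it differs by needle, that difference is part of comparing the needles under the protocol's sequence. This covers the primary comparison and FNA versus FNB within slow pull or within suction.

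**3. Illustration of size.** Every input in this step is assumed.

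- Outcome: heavy blood contamination on a slide. Model: logit P = −0.85 + k·ln(OR) + u, with k = pass number − 1 and u ~ N(0, 1) per lesion. This gives about 33% at pass 1.
- No technique effect.
- McNemar's test at 5%, pass 1 against pass 3. The article does not say which passes are paired.
- 326 patients, from 408 × 0.80 = 326.4; 4,000 simulated trials.

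| Per-pass OR | OR, pass 3 vs 1 (OR²) | False difference | Rejection rate |
|---|---|---|---|
| 1.0 | 1.00 | 0 points | about 5% |
| 1.1 | 1.21 | about 4 points | about 19% |
| 1.2 | 1.44 | about 7 points | about 53% |
| 1.3 | 1.69 | about 10 points | about 84% |

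Repeat runs with other random seeds agreed to within about one percentage point. With all 408 patients the last three rates are about 20–22%, 61–62% and 91–92%. With technique order randomized, rejection stays near 5% throughout.

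A second parameterization gave the same picture: 60% grade A at the median lesion, N = 408, and a shift of −0.25 or −0.5 logit on later passes. The false differences were about 5 and 10 points, with rejection in about 35% and 90% of trials.

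**4. What adjustment for pass number can recover.** Let y1 to y4 be the four pass-level results, each with variance s² and independent given the lesion.

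- Unadjusted: −0.5y1 − 0.5y2 + 0.5y3 + 0.5y4. Variance 4 × 0.25 s² = 1 s². A linear trend of δ per pass adds 2δ to it.
- Adjusted: 0.5y1 − 1.5y2 + 1.5y3 − 0.5y4. The technique coefficient is 1.5 − 0.5 = 1, and the trend coefficient over k = 0, 1, 2, 3 is 0 − 1.5 + 3.0 − 1.5 = 0. Variance (0.25 + 2.25 + 2.25 + 0.25) s² = 5 s².
- Ratio of standard errors: √5 = 2.24.

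The adjusted contrast removes order only if the order effect is linear across the four passes and the same under both techniques. No slow-pull pass is ever third or fourth and no suction pass is ever first or second, so this design cannot test either condition.

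**The case against.** **The objective can be read another way.** The secondary objectives are introduced as FNA-versus-FNB comparisons, and the fourth ends with the word respectively. Read literally, it compares needles within each technique, which is randomized and unconfounded. This stands for the Objectives section. It does not dispose of the point, because Data analysis and the Discussion also plan a direct slow-pull versus suction contrast.

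**The authors promise nothing.** The Discussion qualifies its hope for a clear conclusion with the word hopefully. That is fair: the article states an aim, and the point is only that the design cannot deliver it by this comparison alone.

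**The numbers are illustrative.** This stands in full. The contamination rate, lesion variation, pass pairing and order odds ratios are all assumed. The 20% behind 326 is loss to follow-up, whereas slides are taken at biopsy. Only blood contamination was simulated in the table. A reader might infer that the bias always runs against suction; that follows only from assuming that later passes are worse, and an opposite order effect would favour suction.

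**Adjustment might rescue the contrast.** A reader might infer that a pass-number term settles the matter, since samples are numbered by pass. It does so only under the untestable conditions shown above, so it can serve as a sensitivity analysis but not as the main result.

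**It is late to change the design.** By the Trial status section 372 of 408 patients were enrolled, leaving 36 (36/408 = 8.8%). This limits what randomizing order could achieve. It does not limit a change in how the contrast is labelled and interpreted.

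An unseen analysis plan does not answer the point, because no analysis can restore variation in order that the procedure removed.

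**Conclusion.** The point holds for the direct slow-pull versus suction comparison. That contrast estimates technique plus pass order and cannot by itself support a choice of biopsy method. This follows from the stated sequence and needs no assumed number.

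The practical size is unknown, because the article gives no order effect. Under the assumptions shown, per-pass odds ratios of 1.1 to 1.3 would raise the 5% test's rejection rate to about 19% to 84% with no true technique difference.

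A reader might go further and doubt the trial's main result, or treat all slow-pull and suction data as unusable. The documents do not support that: the primary comparison, and FNA versus FNB within each technique, have identical pass order in both arms. Should-fix, secondary comparison only.

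**What to change.** 1. In Data analysis and the Discussion, define the slow-pull versus suction contrast as exploratory and as technique plus pass order. Drop the claim that it can select a technique.
2. List the fixed order among the limitations in the Discussion, where it is now absent.
3. Add a pass-level sensitivity analysis with a pass-number term, using the existing pass labels. State that it identifies technique only if the order effect is linear and the same under both techniques, that this design cannot test this, and that its standard error is about 2.2 times larger.
4. Where still feasible, randomize technique order 1:1 within needle arm for first biopsies not yet done. This covers at most 36 of 408 patients, needs an amendment because the schedule is already sealed under the scratch cards, and would add little information.

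The cost of items 1 to 3 is a weaker secondary conclusion and a little more analysis. The primary analysis and its sample size do not change.
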